#### Behavioural intervention in the abrupt cessation (control) arm

Participants randomised to abrupt cessation will have a brief discussion about smoking and about the nicotine patch treatment. Participants will be informed that the rationale of wearing the patch is to divorce the cigarette smoking behaviour from its reward (the delivery of nicotine). The relatively high constant level of nicotine is thought to blunt both the pharmacological cue to smoke and the reward from smoking when it occurs. The instruction will therefore encourage the smoker not to reduce consumption at all, even if they feel like smoking fewer cigarettes, because this will work against the stated rationale (not smoking will allow nicotine levels to fall to subnormal (for the participant) levels and create an urge to smoke that will be rewarded by smoking). Patches will be provided for use until the next visit and homework given to identify critical cigarettes, which is the basis for the pre-quit session discussion the next week, used in standard behavioural support. This will be followed by five weekly sessions on quit day and weekly thereafter, following the typical 7-session UK withdrawal orientated therapy programme[30]. Should a participant resume smoking during this treatment, participants will be allowed to renew their quit day following the new NHS standards. From quit day onwards participants in this arm will get combination NRT, meaning patch plus top-up acute product of their choice and be advised to use generous doses of NRT because dose is related to outcome[31] and combination treatment is more effective than patch alone[23]. Combination NRT is standard in our clinics and advised by the National Institute for Health and Clinical Excellence for dependent smokers[32]. Participants will be allowed to choose the type of acute NRT they prefer. Participants will be provided with a diary in weeks 1 and 2 to record the number of cigarettes smoked per day, and whether patches are being used, in week 3 this will be extended to include the amount of acute NRT product used per day.

#### Behavioural intervention in the rapid reduction (intervention) arm

The rapid reduction arm differs from the control arm only in the advice given in the pre-quit period two weeks before quit day. We will offer one of three reduction methods and the participants who do not have a strong preference for one or other method will be allocated at random to one of the three methods. The therapist will have a second set of sealed envelopes to accomplish this prepared as for the main randomisation. The two methods that focus on cigarettes per day will aim to reduce consumption to <50% of baseline at the end of the first pre-quit week and <25% by quit day.

The three methods are as follows:

a) Scheduled reduction (SR) method. In this method, a median inter-cigarette interval is calculated and then this altered so as to achieve the gradual reduction of cigarettes per day. For example, if a person is typically awake for 16 hours per day and smokes 16 cigarettes per day, then the median inter-cigarette interval is 1 hour. To achieve a 50% reduction, the inter-cigarette interval needs to increase to two hours. In this method, a person must smoke every two hours whether or not they want to do so. If they cannot smoke, that cigarette is missed and the next opportunity takes place two hours later. This method is potentially difficult in a country with smoke-free laws and for people with some types of jobs.

b) Hierarchical reduction. There are two variants: hierarchical reduction- difficult (HR-D) and hierarchical reduction- easy (HR-E). In this method, participants classify their usual cigarettes as either habitual cigarettes or particularly rewarding cigarettes. The HR-D method aims to get participants to reduce smoking by removing the difficult cigarettes first. The rationale is that getting rid of the hardest ones is the most difficult and if this can be accomplished well before total abstinence, this will enhance confidence and reduce the chance of a slip. HR-E is similar to HR-D except that participants seek to avoid smoking less rewarding or easier cigarettes to forgo. The rationale is that this gives participants early initial success and allows them confidence to tackle more difficult cigarettes later. If allocated to hierarchical reduction participants will be able to choose whether they will forgo easier of more difficult cigarettes first.

c) Smoke free periods (SFP). This method is different to all other methods in that it does not focus on cigarettes per day as the marker of reduction. In this method, participants map out their typical day, marking the smoking periods of the day. In a country with smoke free laws, smoking behaviour is concentrated into smoking breaks, except perhaps when at home. The SFP procedure will concentrate on reducing the number of smoking periods over the reduction time. In a smoking period, participants will be allowed to smoke as much as they want, but they will not be allowed to smoke outside the smoking period. The rationale is that smokers typically report few urges to smoke in places where smoking is forbidden, but find that not smoking when it is allowed more difficult. This method provides clear boundaries about when smoking is and is not allowed, unlike all other methods that depend on reducing cigarettes per day except perhaps scheduled reduction. It also focuses participants on what is being achieved- smoke free periods- and not on what is being forgone- cigarettes not smoked.

Each participant will complete a diary recording both the target for that day and a report on whether the participant met that target. In methods that focus on cigarettes per day, participants will be asked to put aside the next day's cigarettes into a separate pack to encourage adherence to the target. Participants will be instructed to replace cigarettes missed with a type of acute NRT (for example nicotine gum) and encouraged to use this sufficiently to avoid smoking more cigarettes than quota or smoking in a smoke-free period. Every evening, participants will record cigarettes smoked, acute NRT used (and the remainder in the packet), and note issues in a free text field. In a current trial, we find most participants complete the diary reliably.

### Trial Medication

The trial takes place within the context of NHS smoking cessation clinics, which provide behavioural support and medication to assist smoking cessation. Around 70% of smokers in these clinics use nicotine replacement therapy (NRT) as their medication to assist quitting and this is the only pharmacotherapy that will be available to participants in this trial. Current best practice is to use NRT in combination, which has been endorsed by the Medicines and Healthcare Regulatory Authority as good practice and recommended by the National Institute for Health and Clinical Excellence[32].

In this study, we propose using both nicotine patch and an acute form of NRT in combination (See Table 1). We will use Niquitin, Nicotinell, Wockhardt, and Nicorette NRT products, including 24 hour patches, which are licensed for 16 hour use also (there is no evidence that the effectiveness of 16 hour patches or 24 hour patches is different[33]). These patches provide about 1 milligram (mg) per hour of nicotine. Participants will be advised to wear the patch 24 hours per day, but will be advised to wear it only during day time should they experience sleep disturbance or vivid dreams. Although the medications provide the same amount of nicotine delivery with similar pharmacokinetics, the license dosing advice differs. Niquitin CQ recommend the 21 mg patch for smokers who smoke 10 or more cigarettes per day, while Nicotinell recommend the 30 cm^2 ^(= 21 mg) patch for smokers of 20 or more cigarettes per day. The evidence is that most smokers who smoke 10 or more cigarettes per day get less nicotine from their patch than they did from their cigarettes[34,35]. We have therefore chosen a cut-off of 15 cigarettes per day. In addition, all participants will be offered additional intra-nasal or oral nicotine replacement (gum, microtabs, lozenges, or inhalator) with the choice of delivery system left to personal preference. The dose of these products used will vary, but participants will be advised to take at least 1 mg of absorbed nicotine for each cigarette forgone in the reduction phase because each cigarette delivers about 1.2 mg on average, though this is highly variable[36]. A 2 mg oral product, for example gum, delivers about 1 mg available systemically, and a 10 mg inhalator cartridge yields about 3 mg of nicotine that is systemically available. In the cessation phase, participants in both arms will be given identical dosing instructions and advised to use at least 6 mg of absorbed nicotine daily, which is the minimum dose associated with improved outcomes[33].

**Table 1 T1:** Daily medication regimes

	**Rapid reduction**	**Abrupt cessation**
**Pre-quit period -2 weeks to quit day**	21 mg/24 hour patch, 1 mg of absorbed nicotine per cigarette forgone as a minimum from acute NRT.	21 mg/24 hour patch, No acute NRT.

**Quit day onward**	21 mg/24 hour patch, Minimum of 6 mg of absorbed nicotine from acute NRT. As much as needed to feel comfortable.	21 mg/24 hour patch, Minimum of 6 mg of absorbed nicotine from acute NRT. As much as needed to feel comfortable.

### Rationale of the pre-quit NRT in the abrupt and rapid reduction arms

By utilising pre-quit NRT in both arms we will ensure that any effect is caused by the difference in reduction rather than differences in nicotine intake. Smoking and using a patch gives higher concentrations of nicotine than just smoking, whereas smoking and using an acute form of NRT does not[37]. It is thought that high levels of nicotine dissociate the cigarette from its reward and this is responsible for the effectiveness of nicotine pre-treatment, which is not apparent when acute forms of NRT only are used. Consequently, we have chosen a nicotine patch for both arms. However, gradual reduction could undermine the nicotine pre-treatment effect so we aim to keep nicotine levels high using a patch during reduction and replacing cigarettes with acute NRT.

### Duration of medication use and discontinuation

The license for NRT allows continued use for up to 9 months, but patch use will be phased out using the step down doses between 2 and 3 months after quit day. For participants who are still lapsing but showing determination to stop smoking, the patch will be phased out more slowly, providing no signs of overdose are evident. The dose reduction regimes vary in the summary of product characteristics and in any case the dose reduction is individual, based upon confidence in reducing the patch dose and occurrence of urges to smoke. Oral NRT is commonly continued for several months in abstinent smokers [38-41] and there are reasons to assume this is beneficial, and again we will apply clinical judgement in deciding on length of treatment of oral/intranasal NRT. The advice on patch duration and oral NRT discontinuation will be the same in both arms. At week +8 participants will be given a month supply of NRT and advised to contact either their general practitioner or local stop smoking service should they need further support and/or prescriptions beyond week +12.

### Stopping rules/modification of medication regime

• Participants who have problems with insomnia or difficulties with vivid dreams will use the patch for 16 hours daily, not 24 hours

• Participants who have skin reactions to the patch that are not controlled by switching preparations, emollient and hydrocortisone cream will switch to acute NRT only.

• Participants who become pregnant may have their dose adjusted in line with the National Institute for Health and Clinical Excellence guidance and in accord with the wishes of the participant.

• Participants who show symptoms of overdose will have the dose reduced.

• Participants who fail or give up on their quit attempt will cease using NRT.

### Evidence of safety of smoking whilst using NRT

The safety of using transdermal NRT while smoking was investigated in a review by Fagerstrom & Hughes[37], which is summarised in Table 2. In addition to this review, we have recently systematically reviewed the Cut Down to Stop (CDTS) studies mentioned in the literature review[19]. As part of this, we performed a meta-analysis of adverse events in people smoking and using NRT versus those smoking and using placebo NRT. Overall, 1384 predominantly middle-aged smokers were treated with NRT for 6 to 18 months, while 1383 were treated with placebo. Four deaths occurred in those randomised to NRT and four in those randomised to placebo; Odds ratio (OR) 1.00 95%CI 0.25–4.02. Serious adverse events occurred in fewer than 8% of participants in both arms; OR 1.09 95%CI 0.79–1.50. In no cases were these were judged likely to have been due to treatment. Discontinuation of treatment due to adverse events was rare with 1.7% and 1.3% in the NRT and placebo groups; OR 1.27 95%CI 0.64–2.51. Nausea was selected as an index symptom to indicate possible nicotine overdose. It was slightly and significantly more common in the NRT group with 8.6% versus 5.3% on placebo experiencing nausea; OR 1.69 95%CI 1.21–2.36.

**Table 2 T2:** Summary of Fagerstrom & Hughes review of the safety of smoking and concomitant NRT use[37]

**Study reviewed**	**NRT treatment given**	**Blood nicotine concentrations**	**Safety conclusions**
Foulds et al, 1992	16+ cigarettes per day (cpd) & 15 milligram (mg) transdermal patch (TP) over 16 hrs	Baseline: 37 nanograms per millilitre (ng/ml), Placebo: 36 ng/ml, 15 mg TP: 44 ng/ml.	Participants experienced almost no subjective toxic effects whilst wearing the patch

Pickworth, Bunker & Henningfield, 1994	13+ cpd & 22 mg, 44 mg TP over 24 hrs	Baseline: 30 ng/ml, Placebo: 19 ng/ml, 22 mg TP: 39 ng/ml, 44 mg TP: 63 ng/ml.	No adverse subjective experiences were reported.

Mahmarian et al, 1997	8+ cpd & 14 mg TP over 24 hrs	Baseline 16 ng/ml, 14 mg TP: 24 ng/ml, 21 mg TP: 30 ng/ml.	Only adverse effects noted were nausea & vomiting in 2 patients.

Zevin, Jacob & Benowitz, 1998	Smoking ad libitum & 21 mg, 42 mg, 63 mg patch over 8 hours	Placebo: 20 ng/ml, 63 mg TP: 60 ng/ml.	No additional haemodynamic effects of TP on heart rate, blood pressure, noradrenaline, white blood cell count, fibrinogen, haematocrit, cortisol, or lipids. No adverse reactions.

Carpenter et al, 2000	11+ cpd & TP, gum or inhaler	Lower than 22 mg TP: 54% increase, Higher than 22 mg TP: 190% increase.	Number of cpd reduced by 43% and CO by 31%.

### Lifestyle advice

There is no special dietary or life-style advice that is imposed by using NRT and the associated regimes for using it proposed in the protocol. However, participants using oral NRT will be advised to avoid acidic drinks 15 minutes prior to using oral NRT.

### Concomitant Medication

All medications will be permitted for use concurrently, except those that are proven to help smoking cessation (bupropion, nortriptyline, mecamylamine, reserpine, varenicline), or medications that are unlicensed and for which no interaction data with NRT are available. No rescue therapies will be permitted in treatment, in accordance with the National Institute for Health and Clinical Excellence guidance on smoking cessation pharmacotherapy[32]. The NRT itself is aimed at the relief of symptoms of nicotine withdrawal. Should adverse skin reactions occur with the use of the patch, advice will be given on the use of over the counter emollients and 1% hydrocortisone cream, as is standard. Data on all concomitant medication will be recorded.

### Trial Outcomes

#### Primary trial outcome

• Abstinence at four weeks, measured according to the Russell standard[20,42]. The Russell standard allows a two week grace period from quit day for slips[43].

### Secondary trial outcomes

• Point prevalence at each follow up and prolonged abstinence at 8 weeks and 6 months. Half of those sustaining abstinence for six months sustain it for life, the goal of treatment[44,45].

• Urges to smoke and nicotine withdrawal symptoms will be measured after cessation. Urges to smoke are an important proxy of return to smoking.

### Other trial outcomes (non-efficacy)

• Exhaled carbon monoxide using a CO monitor is a measure of smoke inhalation. We will compare smoke exposure before quit day in both arms of the study.

• Cotinine levels, to show whether nicotine intake rises from normal when smoking in both arms, as we expect, and whether the rise in cotinine relates to the success of treatment. We propose measuring cotinine at baseline, week -1, quit day, and at week +1 on all participants to examine whether reduction leads to higher self-medication with nicotine. It could be that reduction treatment gets people used to using high doses of NRT and therefore some of the effect of treatment could be explained by post-quitting NRT dose. These data will also provide valuable evidence on nicotine consumption while smoking and using NRT.

• Participant rating of the reward from their cigarette while smoking using the modified Cigarette Evaluation Questionnaire (mCEQ)[46,47]. The mCEQ measures satisfaction, taste, mood, cognitive, and sensory sensations to smoking particular cigarettes. Twice each week prior to quitting (to keep participant burden reasonable), we will ask participants to rate satisfaction from smoking from the first cigarette of the day and one other key cigarette. We routinely ask participants to rate cigarette satisfaction in one specimen day so as to anticipate danger periods for lapsing after cessation. Typical rewarding cigarettes are after dinner. Additionally, participants will be asked to rate a cigarette smoked in a negative affect situation. It is possible that the mechanism of benefit may be the reward from smoking, and this study will allow investigation of this. We will also rate satisfaction from smoking after cessation, should slips occur.

• Confidence in quitting is a predictor of abstinence and might be modified by reduction and will be used in mediation analysis. This will be measured by a single question used in other trials that has been shown to predict success. How high would you rate your chances of giving up smoking for good at this attempt? (Circle one response)

Extremely high

Very high

Quite high

Not very high

Low

Very low

• Smoking stereotypy is a measure of the degree to which smoking is prompted by cues to smoke[48]. Perhaps reduction might work by disrupting stimulus control and this scale could measure this. Two questions from this scale will be used to measure smoking stereotypy because the other questions in the scale are either forced to change or could not be assessed over a short period.

There are no specific outcomes proposed when comparing methods of reduction. This analysis will focus on the above measures and is exploratory. See Table 3 for a breakdown of which outcomes are to be measured at specific time-points [49].

**Table 3 T3:** Schedule of trial measures

Follow-up	Trial measures
Baseline (wk -2)	Smoking history, demographics, nicotine dependence using Fagerstrom Test for Nicotine Dependence (FTND)[49], urges and withdrawal (MPSS[51]), confidence in quitting, smoking stereotypy[48], cigarette satisfaction[47], future orientation questionnaire, exhaled carbon monoxide (CO), salivary cotinine, Give out diaries.

Pre-quit visit (wk -1)	CO, cotinine, MPSS, confidence, smoking stereotypy, cigarette satisfaction, adverse events. Collect diaries with daily smoking, NRT use, MPSS urge questions. Give out diaries.

Extra pre-quit visit (wk -1a)	**Only applicable if delays quit date by 1 week** CO, MPSS, confidence, smoking stereotypy, cigarette satisfaction, adverse events. Collect diaries with daily smoking, NRT use. Give out diaries.

Extra pre-quit visit (wk -1b)	**Only applicable if delays quit date by 2 weeks** CO, MPSS, confidence, smoking stereotypy, cigarette satisfaction, adverse events. Collect diaries with daily smoking, NRT use. Give out diaries.

Quit day (wk 0)	CO, cotinine, MPSS, confidence, smoking stereotypy, cigarette satisfaction, adverse events. Collect diaries with daily smoking, NRT use, MPSS urge questions. Give out diaries.

One week after quit day (wk +1)	CO, cotinine, MPSS, confidence, cigarette satisfaction if lapsed, adverse events Collect diaries with daily smoking, NRT use, MPSS urge questions

Post-quit visits (wks +2, +3, +4)	Smoking in past week, CO, MPSS, confidence, cigarette satisfaction if lapsed, future orientation questionnaire at week 4, amount NRT used, adverse events

+8 wk visit	Smoking in past 4 weeks, CO, MPSS, cigarette satisfaction if lapsed, confidence, amount NRT used, adverse events

6-month telephone call	Smoking status over past 5 months, use of NRT. Those claiming 7-day abstinence will be invited to a validation visit for exhaled CO and to complete the future orientation questionnaire. Serious adverse events (SAEs)

In addition to the weekly clinic measures, participants will complete a daily diary for the first three weeks of the trial from week -2 to week +1. This will record whether or not the patch is worn, the amount of acute NRT used, the number of cigarettes smoked, and the two urge to smoke questions from the Mood and Physical Symptoms Scale (MPSS). Once a week, the diary will include the mCEQ, with the other measure being taken in clinic.

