### Withdrawal criteria

Trial Withdrawal: It is standard practice in smoking cessation trials to regard those who fail to attend for support and treatment as having relapsed, which is based on some evidence[20]. Therefore, failure to attend will not count as withdrawal from the trial and the only withdrawals will be those where a patient asks to be withdrawn. Such patients will not be replaced and, unless s/he refuses permission, data available up to that point will be used. Such withdrawals are expected in fewer than 5% of participants. This is standard procedure in smoking cessation studies.

Treatment withdrawal: One of our exclusion criteria is previous adverse reactions to NRT; so given that most smokers have used NRT recently, the established safety profile of NRT and the evidence from trials of combination NRT, we do not expect any serious adverse events due to the medication. Nevertheless, there will be a detailed work instruction for the trial that will detail the weekly assessment of side-effects, and the procedure for serious adverse events (SAE) and suspected unexpected serious adverse reactions (SUSARs). In the event of an SAE or SUSAR that is judged either possibly, probably, or definitely related to NRT, the prescription for NRT will be withdrawn and not re-instituted in that person.

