#### Monitoring and audit

The progress of the trial will be monitored by quarterly review of records. This will ensure that consent is being obtained and the inclusion and exclusion criteria are adhered to. The medication dispensed and the instructions for using it will also be assessed.

Data cleaning will take place by a series of logical checks on the electronic data. (For example, a person cannot be recorded as prolonged abstinent smoker at 6 months if they were not in such a state at 8 weeks). Discrepant records will be checked with the source documents and the database amended if necessary.

The trial will be potentially subject to audit by the appropriate regulatory authorities and therefore participants will be asked to consent to allow their records to be viewed.

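### At week +4 the smoking question reaches back one week, but the primary outcome depends on two, so a missed week +3 visit leaves half the window unobserved

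*Protocol article*

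**What the plan says.** The protocol article defines the primary outcome under Primary trial outcome as "Abstinence at four weeks, measured according to the Russell standard", and adds that "The Russell standard allows a two week grace period from quit day for slips".

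Table 3 (Schedule of trial measures) sets the smoking questions:
- Weeks +2, +3 and +4 share one entry: "Smoking in past week, CO, MPSS, confidence, cigarette satisfaction if lapsed".
- Week +8: "Smoking in past 4 weeks, CO, MPSS, cigarette satisfaction if lapsed".
- 6-month call: "Smoking status over past 5 months, use of NRT".

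The text below Table 3 says that "participants will complete a daily diary for the first three weeks of the trial from week -2 to week +1".

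Participant Recruitment sets weekly visits up to four weeks after quit day. On non-attendance, Withdrawal criteria calls it standard practice to "regard those who fail to attend for support and treatment as having relapsed". Power calculation says that those lost to follow-up are taken to be smokers. Neither section says how to classify someone who misses one interim visit and then attends the next.

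**The concern.** The recall at week +4 matches the gap between scheduled visits, not the window that defines the primary outcome. The third week after quit day is asked about at one visit only. A participant who misses that visit and returns at week +4, reporting no smoking and with a CO reading that agrees, has no recorded smoking status for half of the decisive period.

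Either way of scoring that person has a cost. Scored as relapsed, a true abstainer becomes a failure because of attendance. Scored as abstinent, any smoking in the third week goes uncounted. An analysis rule can choose between these, but it cannot recover an answer that was never requested. In a non-inferiority trial with a margin in percentage points, misclassification that lowers the rate in both arms also compresses the difference between them, which makes non-inferiority easier to declare.

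**Working it through.** **1. The plan's own figure.** Inputs from Power calculation: 50% abstinence in both arms, margin 9.5 points, one-sided alpha 0.05, power 80%. With unpooled variance:

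n per arm = (1.645 + 0.842)² × 2 × 0.5 × 0.5 / 0.095² = 3.09 / 0.009025 ≈ 342.5, so 343.

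This reproduces the stated 343 per arm. The same formula with a 5-point margin gives 1,237 per arm, or 2,474 in total, against the stated 2,500. The sample size is not in question.

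**2. Coverage of the outcome window.** Take quit day as day 0 and assume that visits fall on schedule. With a 14-day grace period the window is days 15 to 28, which is 14 days.

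| Instrument | Days covered | Days inside the window |
|---|---|---|
| Daily diary | up to about day 7 | 0 |
| Week +2, past week | 8–14 | 0 |
| Week +3, past week | 15–21 | 7 |
| Week +4, past week | 22–28 | 7 |
| Week +8, past 4 weeks | 29–56 | 0 |
| 6-month call, past 5 months | from about week +4 | about 0 |

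- All visits attended: 14 of 14 days covered.
- Week +2 missed: still 14 of 14.
- Week +3 missed, week +4 attended: 7 of 14, with days 15 to 21 covered by nothing listed.

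Table 3 states no look-back to days 15 to 21 for the week +4 CO reading or for the satisfaction item asked of those who lapsed.

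**3. Illustration if the gap is scored as relapse.** Assumption, because the documents give no rate: in both arms a share m of true abstainers misses week +3, attends week +4 and is scored as relapsed. The true rates are 50% (abrupt) and 40.5% (reduction), a deficit equal to the margin.

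Recorded rates are 0.50(1 − m) and 0.405(1 − m), so the recorded deficit is 0.095(1 − m). At 350 per arm (the planned 700), the probability of declaring non-inferiority is Φ[(0.095 − recorded deficit)/SE − 1.645], with SE from the two recorded rates.

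| m | Recorded rate, abrupt | Recorded deficit | Chance of declaring non-inferiority |
|---|---|---|---|
| 0 | 50% | 9.5 points | 5.0% |
| 5% | 47.5% | 9.0 points | 6.5% |
| 10% | 45% | 8.6 points | 8.3% |
| 20% | 40% | 7.6 points | 13.1% |

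The ratio 0.405/0.50 = 0.81 does not change with m. The drift arises because the margin is an absolute difference.

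**4. If the gap is scored as abstinent.** Third-week smoking in these participants is not counted. The documents give nothing from which to size this.

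**The case against.** The planned schedule has no hole. Visits are weekly to week +4, and each recall from week +2 to week +8 runs back to the previous visit. That is true, and it makes the gap conditional on a missed visit. Table 3 is also a condensed schedule, and the case report form may ask more. But the table does state a recall period, and that period does not fit the outcome window. Choosing a scoring rule can be left to an analysis plan; collecting the answer cannot.

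A reader might infer more than the documents support:

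- **That one missed visit is scored as relapse.** The sentence in Withdrawal criteria explains why non-attendance is not counted as withdrawal. It does not clearly fail someone for one missed interim visit, and a participant seen and CO-tested at week +4 is not clearly lost to follow-up. Scoring is referred to the Russell standard, whose text is not at hand.
- **That attendance will differ between arms and create a false difference.** Unequal misses of 5% and 10% would give 50% × (0.95 − 0.90) = 2.5 points. But the section on the rapid reduction arm says that the arms differ only in pre-quit advice. Differential attendance at week +3 is possible in an unblinded trial, but nothing in the documents points to it.
- **That week +8 is better designed.** Its four-week recall also reaches only to the previous visit, so a missed week +4 leaves the same kind of gap there.
- **That a missed 8-week visit bars 6-month abstinence.** Monitoring and audit says that "a person cannot be recorded as prolonged abstinent smoker at 6 months if they were not in such a state at 8 weeks", but gives this as an example of a data-cleaning check. Discrepant records are then compared with source documents. It is not an outcome rule for missed visits.

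**Conclusion.** The point holds in a limited form. For a participant who misses week +3 and attends week +4, the listed instruments cover 7 of the 14 days that decide the primary outcome. With full attendance there is no gap.

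The day count follows from the text, given visits on schedule. The size of the effect does not, because no missed-visit rate is stated. The illustrative range (recorded abstinence of 47.5% to 40% instead of 50%, and a 9.5-point deficit recorded as 9.0 to 7.6 points) rests on three assumptions: a rate of 5% to 20% among true abstainers, the same rate in both arms, and scoring as relapse. Under those assumptions the error runs towards non-inferiority. The documents do not support a claim of bias between arms or a defect in the 8-week and 6-month outcomes on this ground.

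**What to change.** At week +4, ask about any smoking since the end of the grace period, that is, the past two weeks. Score the primary outcome on all available reports plus the week +4 CO reading: smoking in the window reported at either week +3 or week +4 counts as failure, and a missed week +3 visit alone does not. Keeping the week +3 report matters, because scoring on the week +4 answer alone would discard smoking already reported.

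A participant who misses week +3 and attends week +4 then has 14 of 14 days covered. The sample size stays at 343 per arm. The cost is one changed recall period on the week +4 form and one sentence on classification. The downside is two-week instead of one-week recall for those who missed week +3. If the case report form already asks about the longer period, only the Table 3 entry and the classification sentence need to change.
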